### Sample size

The sample size calculation is based on a between-group comparison of the mean change in HAM-D-17 scores from baseline to day 20. Analysis of covariance (ANCOVA) will be used, with the change in HAM-D-17 score from baseline to day 20 as the outcome and baseline HAM-D-17 score and sex as covariates. In our previous pilot study [16], involving 10 participants with moderate to severe MDD who received three FES sessions per week (ranging from a minimum of 10 to a maximum of 40 total sessions), FES demonstrated a moderate to large effect size (d = 0.6–1.2) in MDD. All 10 participants completed the required 10 sessions, and 5 participants completed 40 sessions [16]. Our RCT will use 20 sessions of FES, which was well tolerated in research on rTMS for MDD and FES for stroke and spinal cord injury rehabilitation.

A total of 60 participants (30 in the active arm and 30 in the sham arm) is planned to detect a clinically meaningful between-group difference in HAM-D-17 scores, assuming a moderate effect size of 0.5 (Cohen’s d), a two-tailed significance level of 0.05, and 80% power. Accounting for a 15% attrition rate, approximately 51 participants are expected to complete the study, exceeding the recommended minimum sample size (24–50 participants) needed to generate reliable estimates of the standard deviation and correlation of HAM-D-17 scores for future sample size calculations in a definitive trial. Furthermore, a sample size of 60 will allow the anticipated 15% dropout rate to be estimated with an approximate 95% confidence interval margin of error of ±8.4. As the first proof-of-concept RCT of its kind, this trial is designed primarily to detect a signal for the primary outcome, change in HAM-D-17 over time. We recognize that the proposed sample size may not provide high statistical power for some secondary and exploratory outcomes.

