A neural feedback loop has been proposed in which facial muscle activity influences emotional processing through the amygdala, a key structure involved in emotion processing and generation [15]. Facial motor activity is conveyed to the amygdala, which integrates proprioceptive signals from the trigeminal nerve and interoceptive signals carried through the glossopharyngeal and vagus nerves [15]. By activating the facial muscles, FES may engage these pathways and contribute to neuroplastic changes involved in emotional regulation.

Zariffa et al. (2014) [14] conducted a pilot study exploring the mood-related effects of a single FES session targeting the Duchenne smile muscles in healthy individuals. Twelve participants receiving FES were compared with 12 controls. Based on the Positive and Negative Affect Schedule-X (PANAS-X), the findings suggested that FES may influence emotional states such as feeling “determined,” “daring,” “scared,” and “concentrating.” Building on this initial study, Kapadia et al. (2019) [16] conducted an open-label trial with MDD patients and reported significant improvements in depressive symptoms following a treatment course with FES, with participants showing an 8.1-point reduction on the 17-item Hamilton Depression Rating Scale (HAM-D-17) and a 14-point reduction on the Inventory of Depressive Symptomatology after 10 sessions of FES. Moreover, evidence from studies on Facial Neuromuscular Electrical Stimulation (fNMES), which directly activates facial muscles using computer-controlled electrical impulses, also supports an effect of facial muscle activation on emotional experience [17,18]. Participants reported more positive emotions after stronger stimulation of the zygomaticus major (smile muscle) compared to the depressor anguli oris (frown muscle) [18]. These studies provide promising evidence for the therapeutic potential of FES for MDD, setting the stage for designing a rigorous randomized sham-controlled trial (RCT) examining the efficacy of repetitive FES of facial muscles for MDD. This pilot RCT will assess the efficacy, safety, and tolerability of 20 sessions of FES in 60 participants diagnosed with MDD using a sham-controlled design.

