### Intervention

Participants will receive transcutaneous FES targeting the bilateral zygomaticus major and orbicularis oculi muscles with self-adhesive surface electrodes placed on all four muscles (Fig 3). Each FES session, whether active or sham, will last for 60 minutes, comprising 15 minutes of preparation and 45 minutes of stimulation. FES will be administered using the Twin Stim® Plus Digital TENS/EMS FES device (Health Canada License name: TWIN STIM SERIES), providing 300 μs charge-balanced biphasic pulses at 40 Hz. During the intervention sessions, participants will watch a comedy video designed to elicit genuine Duchenne smiles while being instructed to intentionally produce a Duchenne smile at least once per minute. All intervention visits will be video recorded.

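### The only effect size cited in the sample-size section (d = 0.6–1.2) comes from an open-label pilot with no control arm described, so it neither confirms nor excludes the between-group d of 0.5 on which the trial is sized

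*Protocol article*

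**What the plan says.** The Sample size section of the protocol article bases the calculation on the difference between arms in mean HAM-D-17 change from baseline to day 20. The analysis is ANCOVA, adjusted for baseline score and sex. Before giving the number, the section turns to the group's previous pilot of 10 participants with MDD, who had between 10 and 40 sessions, and states that "FES demonstrated a moderate to large effect size (d = 0.6–1.2) in MDD". The next paragraph gives the size: "A total of 60 participants (30 in the active arm and 30 in the sham arm) is planned", and these 60 are "planned to detect a clinically meaningful between-group difference in HAM-D-17 scores, assuming a moderate effect size of 0.5", with "a two-tailed significance level of 0.05, and 80% power". With 15% attrition, about 51 completers are expected.

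The Introduction describes the pilot's design. Its investigators "conducted an open-label trial with MDD patients and reported significant improvements in depressive symptoms", with an 8.1-point fall on the HAM-D-17 after 10 sessions and a fall on a second depression scale. No control group is mentioned. For the separate healthy-volunteer study, the same section does mention 12 controls. The Discussion describes the present trial as, to the authors' knowledge, the first randomised trial of FES in MDD.

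In the Intervention section, sham is an attended 60-minute session with low-level stimulation. The session description does not separate the arms: "participants will watch a comedy video designed to elicit genuine Duchenne smiles", and they are told to produce such a smile at least once a minute. No expected sham change is stated anywhere.

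**The concern.** An effect size from one treated group and an effect size between two randomised groups measure different things. The first contains whatever participants would have gained without the active component: placebo response, staff contact, natural course and regression to the mean. The second has these removed by the comparison with sham. The two may also be divided by different standard deviations, since a before-after d can use the SD of the change or the baseline SD.

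Here the uncontrolled figure stands directly before the between-group assumption, is not labelled as uncontrolled, and has no sham deduction. A reader sees 0.5 just below 0.6–1.2 and may take it as a cautious choice backed by data. The Success criteria section requires a statistically significant active–sham difference, so the expectation set here will colour how the result is read. A null result could be judged against an expectation that had no between-group evidence behind it.

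**Working it through.** **Inputs.** From the Sample size section: d = 0.5, two-sided alpha 0.05, 80% power, 30 per arm, about 51 completers, pilot d = 0.6–1.2 in 10 participants. Not in the document: any sham response, SD, or baseline/follow-up correlation.

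**1. The plan's own figure.** Unadjusted, n per arm = 2(1.960 + 0.842)² / 0.5² = 62.8, so 63 per arm and 126 in total. Allowing for 15% dropout gives 126 / 0.85 = 148.2, so 149. The stated 60 is not reproduced. That mismatch is a separate matter. It enters here only because the 80% figure has to be replaced.

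**2. Power at N = 60 over a range of effects.** Two-sample t-test, two-sided 0.05, noncentrality = d × √(n/2). With n = 30, √15 = 3.873 and df = 58.

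| Between-group d | Noncentrality | Power |
|---|---|---|
| 0.30 | 1.16 | 21% |
| 0.50 | 1.94 | 48% |
| 0.60 | 2.32 | 63% |
| 0.72 | 2.79 | 78% |

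With 51 completers (25.5 per arm on average), d = 0.5 gives noncentrality 0.5 × √12.75 = 1.79 and power 42%.

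**3. How much sham improvement would leave d = 0.5?** Assume that the pilot d is on the between-group SD scale and that sham achieves a share s of the active before-after change. Then between-group d = pilot d × (1 − s), and the break-even share is s = 1 − 0.5 / pilot d:
- pilot d 0.6: 1 − 0.833 = 17%
- pilot d 0.9 (mid-range): 1 − 0.556 = 44%
- pilot d 1.2: 1 − 0.417 = 58%

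**4. Illustrative sham shares.** The 40–60% range is an assumption.

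| Sham share | Between-group d | Power, 30 per arm |
|---|---|---|
| 40% | 0.36–0.72 | 28%–78% |
| 50% | 0.30–0.60 | 21%–63% |
| 60% | 0.24–0.48 | 15%–45% |

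The value 0.5 lies inside the first two ranges and just above the third. The pilot therefore does not settle the question either way.

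**5. Pilot precision.** If the pilot d is a paired standardised change in 10 people, the 95% interval is about −0.09 to 1.26 around 0.6 and 0.36 to 2.01 around 1.2. The figure is imprecise even before any sham deduction.

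**6. Covariate adjustment.** ANCOVA multiplies the residual variance by (1 − ρ²), where ρ is the baseline/follow-up correlation. By normal approximation, the d detectable with 80% power unadjusted is 2.802 × √(2/30) = 0.723 with 60 analysed and 2.802 × √(2/25.5) = 0.785 with 51. For d = 0.5 to reach 80% power, ρ must be √(1 − (0.5/0.723)²) = 0.72 with 60, or √(1 − (0.5/0.785)²) = 0.77 with 51. No correlation is stated, and the section lists it among the quantities that this trial should help to estimate.

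**The case against.** The strongest reply is that the section only assumes 0.5 and never derives it. The pilot figure sits in a separate paragraph, next to session counts and tolerability, and 0.5 may be a conventional or target value. This stands. A reader might infer that the sample size was computed from the pilot, and the documents do not support that. What remains is narrower: no other effect size, minimum important difference in points, or SD is offered, so the pilot is the only evidence that a reader can set beside 0.5.

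A second reply is that 0.5 lies below the pilot range and so already includes a discount. A reader might counter that 0.5 is cautious only if sham hardly improves. That is true only at the lower end, where the room is 17% of the active change. At 0.9 and 1.2 the room is 44% and 58%. So the documents do not show that 0.5 is too optimistic. Equally, no discount is stated or justified.

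It is also tempting to turn the pilot into points. The 8.1-point fall would imply an SD of 8.1 / 1.2 = 6.75 at one end of the range and 8.1 / 0.6 = 13.5 at the other. The document does not say which scale, time point or number of sessions lies behind either end, so no such conversion is safe. For the same reason one cannot say that the range reflects 40-session courses.

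Finally, the section calls the trial a proof-of-concept study and gives estimation reasons for 60 participants. Those reasons support keeping N. They do not support the 80% power claim, or the pilot d as evidence for a difference from sham.

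**Conclusion.** The point holds in a limited form. The sample-size section offers an uncontrolled effect size as the only empirical backdrop to a between-group assumption. That figure neither confirms nor excludes d = 0.5. This conclusion rests only on the pilot as the protocol describes it: open-label, 10 treated participants, no control arm mentioned. It does not depend on any sham share or SD.

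The consequence is that the stated expectation is firmer than the evidence allows. Across between-group effects from 0.3 to 0.72, unadjusted power at 30 per arm runs from about 21% to 78%. It is 48% at the assumed 0.5, and 42% if 51 complete. These figures ignore covariate adjustment, which would raise them by an amount that depends on an unstated correlation. The sham shares of 40–60% are illustrative, and applying them requires the pilot d to be on the between-group SD scale, which is unknown.

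The point concerns the justification and how a result will be read. It is not an error in the planned analysis. It should be corrected, and it gives no reason to stop or enlarge the trial.

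**What to change.** Rewrite the effect-size and power statements in the Sample size section:

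1. Label d = 0.6–1.2 as an uncontrolled effect from an open-label pilot, giving its scale, time point and standardiser. Do not offer it as support for the active–sham difference.
2. Present 0.5 as a target difference, with the assumed SD and the assumed HAM-D-17 change in each arm, including sham.
3. Replace the single 80% claim with power at N = 60, and at 51 completers, over a range of between-group effects such as 0.3 to 0.72. Show any gain from ANCOVA with the correlation assumed for it.
4. Keep N = 60, on the proof-of-concept and estimation grounds that the section already gives.

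The cost is one paragraph and a less favourable stated expectation. No participants, visits or analyses are added. The requirement of a significant difference in the Success criteria is not changed by this edit, but it would then be read against realistic power.

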### Randomization and masking

Participants will be randomly assigned in a 1:1 ratio to receive either active FES or sham using a randomization schedule generated through a secure REDCap module. Block randomization, stratified by sex, will account for potential differences in response and tolerability. Personnel conducting outcome assessments and other blinded study procedures will not have access to the fixed block size or treatment assignments. Randomization will be conducted by the intervention staff, who will have access to group assignments as required to deliver and monitor the stimulation sessions. In an emergency, the study doctor may be informed of the participant’s group assignment if this information is necessary for clinical management.

Moreover, to preserve blinding, sensory and non-Duchenne-patterned sham stimulation will be utilized. Participants will be instructed to avoid interaction with one another throughout the study. Blinding effectiveness will be assessed after each session by asking participants and raters to indicate whether they believe the participant received active or sham FES.

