### Success criteria

The success of this study will be assessed quantitatively based on the achievement of its primary and secondary objectives. Success will be evaluated across three domains: efficacy, tolerability, and safety, based on changes in HAM-D-17 scores, participant retention and protocol adherence, and the frequency and nature of AEs and SAEs. Specifically, success will be indicated by a clinically meaningful reduction in HAM-D-17 scores, defined as a reduction of ≥50% from baseline, in the active FES group. Additionally, a statistically significant difference in HAM-D-17 score changes between the active and sham groups will be required. Successful tolerability will be demonstrated by a dropout rate of ≤15% and high adherence to the treatment protocol, with at least 85% of participants completing all scheduled FES sessions.

For safety outcomes, the number, nature, and duration of AEs will be evaluated in both active and sham groups, and no significant differences between groups in AE frequency or severity will indicate successful safety outcomes. Additionally, the sustainability of observed treatment effects will be assessed by analyzing HAM-D-17 response and remission rates, as well as changes in secondary outcomes, including anxiety (GAD-7), quality of life (WHO-5), and sleep quality (PSQI) over the four-week follow-up period. Sustained improvements across these domains in the active group, without significant increases in adverse effects, will further validate the success of the study.

If these success criteria are met, the findings will provide a robust foundation for designing a large-scale, multisite RCT to further evaluate FES for MDD.

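### The stated 80% power for d = 0.5 with 30 per arm does not follow from the printed inputs: unadjusted power is about 48% (about 42% with 51 completers), and the planned ANCOVA reaches 80% only under a high correlation that the article does not state

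*Protocol article*

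**What the plan says.** All the inputs are in the protocol article.

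- **Comparison** (Sample size): "The sample size calculation is based on a between-group comparison of the mean change in HAM-D-17 scores from baseline to day 20".
- **Model** (Sample size, repeated in Data analysis plan): ANCOVA with "baseline HAM-D-17 score and sex as covariates". The article gives no baseline-to-outcome correlation and no variance reduction.
- **Size and allocation**: "A total of 60 participants (30 in the active arm and 30 in the sham arm) is planned" (Sample size), with 1:1 randomization (Randomization and masking).
- **Effect, alpha, power** (Sample size): "assuming a moderate effect size of 0.5 (Cohen’s d") and "a two-tailed significance level of 0.05, and 80% power".
- **Attrition** (Sample size): 15%, so that "approximately 51 participants are expected to complete the study". This figure is then set against a recommended minimum of 24–50 for estimating the SD and correlation of HAM-D-17.
- **Success rule** (Success criteria): "a statistically significant difference in HAM-D-17 score changes between the active and sham groups will be required". A reduction of at least 50% in the active arm is asked for as well.

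The Sample size section also describes the trial as looking for a signal on the primary outcome. It concedes limited power only for some secondary and exploratory outcomes.

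**The concern.** The power statement is complete: effect, alpha, sidedness, arm sizes and power are all printed, so it can be checked. A standardized difference of 0.5 at two-sided 0.05 ordinarily needs a little over 60 per arm for 80% power, and the plan has half that. Attrition is then taken off the 60; the 60 was not inflated to allow for it.

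What is at stake is how the primary result will be judged. Statistical significance is a condition of success, and meeting the success criteria is described as the foundation for a multisite trial. If power is near one half, a true effect of the planned size has a large chance of failing that condition, and nothing in the article tells the reader so.

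**Working it through.** **Inputs.** d = 0.5, two-sided alpha 0.05, 30 per arm (60), about 51 completers (60 × 0.85 = 51, taken as 25 and 26), all from Sample size. The correlation r between baseline and day-20 HAM-D-17 is not stated, so every value of r below is an assumption.

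**1. The plan's own figure, unadjusted.** The noncentrality is d × √(n₁n₂/(n₁+n₂)), referred to a noncentral t with n₁+n₂−2 degrees of freedom.

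- 30/30: 0.5 × √15 = 1.936; 58 df; critical value 2.002; power **47.8%**. The normal approximation gives Φ(1.936 − 1.960) = 49.1%.
- 25/26: 0.5 × √(650/51) = 1.785; 49 df; critical value 2.010; power **41.7%**.

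The stated 80% is not reproduced.

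**2. Size needed for 80%.** Normal approximation: 2 × (1.960 + 0.842)² / 0.5² = 62.8, so 63 per arm. The t distribution gives 63.8, so **64 per arm, 128 evaluable**. With 15% dropout, 128/0.85 = 150.6, or 151 randomized.

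**3. Effect detectable with 80% power, unadjusted.** d = **0.74** with 60 and **0.80** with 51.

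**4. Other readings that might yield 80%.**

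| Reading | Power |
|---|---|
| One-sided 0.05, 30/30 | 60.6% |
| Two-sided 0.10, 30/30 | 60.6% |
| Two-sided 0.20, 30/30 | 74.0% |
| 60 per arm (contradicts the stated 30) | 77.5% |
| Paired test, n = 30 (not the stated comparison) | 75.4% |

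A paired test with n = 60 gives 96.8%, but that too is not a between-group comparison. None of these gives 80%.

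**5. ANCOVA, d in raw-score SD units.** The residual variance factor is 1 − r². The noncentrality is d/√(1 − r²) × √(N/4), with N − 4 df (two covariates). Example, r = 0.5, N = 60: 0.5/√0.75 × √15 = 2.236; 56 df; power 59.4%.

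| Assumed r | N = 60 | N = 51 |
|---|---|---|
| 0.3 | 51% | 45% |
| 0.5 | 59% | 52% |
| 0.6 | 66% | 59% |
| 0.7 | 76% | 69% |

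Reaching 80% needs r of about **0.73** (N = 60) or **0.78** (N = 51).

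**6. ANCOVA, d in change-score SD units.** The article bases the calculation on mean change, so this reading is open too. With equal variances at both times, the change-score variance is 2(1 − r) and the ANCOVA residual variance is 1 − r², both in units of the raw-score variance. Their ratio is (1 + r)/2, and the noncentrality is d/√((1 + r)/2) × √(N/4). At r = 0, N = 60: 0.5/√0.5 × √15 = 2.739, power 76.8%.

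| Assumed r | N = 60 | N = 51 |
|---|---|---|
| 0 | 77% | 70% |
| 0.3 | 66% | 58% |
| 0.5 | 59% | 52% |
| 0.7 | 54% | 47% |

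Here power falls as r rises, so no non-negative correlation reaches 80%. The two readings coincide at r = 0.5, where both variance factors equal 0.75.

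**The case against.** Several points on the other side are sound and limit the claim.

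- **The trial will run ANCOVA, not an unadjusted test.** This stands. The 48% and 42% are unadjusted figures and must be labelled so; the ANCOVA range belongs beside them.
- **The correlation may be in the full protocol.** The article points to it as a supplementary file, which is not shown. This stands: leaving a correlation out of an article is not itself the fault. The fault is that 80% does not follow from the inputs printed. The 0.73 and 0.78 thresholds also apply only if d is in raw-score SD units.
- **The analysis set may exceed 51.** This stands. The modified ITT set includes everyone with at least one session, and HAM-D-17 is collected weekly, so some dropouts may contribute. The 42% is a completers-only figure. The article uses the 51 to support SD and correlation estimation, not power.
- **It is a pilot seeking a signal.** This does not remove the error, because 80% is stated outright for the primary comparison. The larger pilot effects (d = 0.6–1.2) do not help either: the plan chose 0.5, and even d = 0.6 gives only 63% (60) or 56% (51) unadjusted.

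A reader might also infer that the trial exists in order to estimate the correlation, so that the correlation could not have been a planning input. The article does not say that. It says the completers exceed a minimum recommended for such estimates, and that the main design aim is a signal on the primary outcome.

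**Conclusion.** The 80% figure is wrong as written. With the stated inputs, unadjusted power for d = 0.5 is about 48% with 60 participants and about 42% if only 51 contribute. Under ANCOVA with assumed correlations of 0.3 to 0.6 and d in raw-score SD units, it is 51–66% (60) or 45–59% (51). With d in change-score SD units and equal variances, it is at most 77% or 70%.

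The article's significance condition would therefore be missed 52–58% of the time on the unadjusted figures (100 − 48 and 100 − 42) when d = 0.5 is true, and about 41–48% of the time under ANCOVA with r = 0.5 (100 − 59 and 100 − 52). Joint efficacy success cannot be more likely than meeting this one condition, because the active-arm reduction is required as well.

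Two stronger readings are not supported. One is that the trial is more likely than not to fail its significance condition: that depends on the correlation, and at r = 0.6 with 60 evaluable and d in raw-score SD units, power is 66%. The other is that a significance criterion is itself an error in a pilot: that is a design choice, and only the power figure attached to it is wrong.

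**What to change.** Keep 60 participants and correct the text.

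- **Sample size.** Replace the 80% statement with the actual figures: 80% power for d of about 0.74 with 60 evaluable or 0.80 with 51, unadjusted; for d = 0.5, power of about 48% or 42% unadjusted, and about 59% or 52% under ANCOVA with an assumed correlation of 0.5. State the correlation assumed, and whether d is in raw-score or change-score SD units. If the full protocol holds a justified correlation, print it and give the power that follows from it.
- **Justification of the size.** Rest it on the precision grounds already in the same section (estimating the SD, the correlation and the dropout rate), and extend the concession about limited power to the primary comparison.
- **Success criteria.** Beside the significance condition, state the probability of meeting it when d = 0.5 is true, under the stated correlation. The condition itself need not change.

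The cost is wording in two sections and a less favourable stated power. No more participants are needed. Recruitment is expected to run to June 2028, so the correction can be made well before results.

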### Data analysis plan

Baseline demographic and clinical characteristics will be summarized for each treatment group. The primary analyses will be conducted on a modified intention-to-treat (ITT) sample, including all randomized participants who received at least one FES session. The efficacy of FES will be evaluated using ANCOVA to compare changes in HAM-D-17 scores from baseline to the final FES session between the active and sham groups, adjusting for baseline HAM-D-17 score and sex. Correlations between baseline and follow-up HAM-D-17 scores will be analyzed at the participant level. Similar analyses will be conducted for secondary clinical outcomes. Moreover, FES tolerability will be evaluated by summarizing overall dropout rates as counts and percentages. For dichotomous outcomes like remission, response, and AEs, between-group differences will be analyzed using odds ratios with 95% confidence intervals. Blinding effectiveness will be assessed by calculating Bang’s blinding index for rater and participants. Analyses stratified by sex and age will also be performed to explore potential subgroup differences.

Additionally, automated facial behavior analysis software (OpenFace) will be used to quantify Duchenne smile metrics derived from facial Action Units (AUs), including frequency, duration, and average activation intensity. Duchenne smiles will be identified based on the concurrent activation of AU12 (lip corner puller) and AU6 (cheek raiser). Descriptive statistics and group comparisons will be performed to examine differences in genuine smiling between the FES and sham groups. OpenFace is an open-source facial behavior analysis toolkit developed by researchers at the University of Cambridge and Carnegie Mellon University. Using computer vision and machine learning algorithms, it detects facial landmarks (e.g., eye, mouth, and eyebrow positions), estimates head pose, and quantifies facial muscle activity through the Facial Action Coding System (FACS) by identifying the presence and intensity of facial AUs. Participant videos will be processed using OpenFace to extract facial landmark coordinates and AU measurements. The output will consist of CSV files containing numerical facial behavioral data identified only by participants’ study IDs. These de-identified data will subsequently be used for statistical analysis.

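### The ±8.4 margin of error quoted for a 15% dropout rate in 60 participants should be ±9.0 percentage points

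*Protocol article*

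**What the plan says.** The Sample size section plans 60 participants, 30 per arm, and expects 15% attrition: "Accounting for a 15% attrition rate, approximately 51 participants are expected to complete the study". It then adds a statement of precision. With all 60 participants, the plan expects "the anticipated 15% dropout rate to be estimated with an approximate 95% confidence interval margin of error of ±8.4". The text as read shows no unit after 8.4; percentage points is the natural reading.

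Dropout appears in three other places. Outcome measures and data collection lists it among the tolerability and safety measures that form the second primary outcome. The Data analysis plan says that "FES tolerability will be evaluated by summarizing overall dropout rates as counts and percentages". Success criteria says: "Successful tolerability will be demonstrated by a dropout rate of ≤15" per cent. It names no arm and attaches no confidence interval.

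**The concern.** The precision sentence is self-contained: rate, sample size and confidence level are all stated, so a reader can recompute the margin in one line. The result is larger than the printed figure.

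The sentence is one of the grounds offered for a sample of 60, and it describes a component of a primary outcome. The trial is also meant to inform a larger multisite trial, so its precision statements may be reused. At stake is an accurate account of how well 60 participants can estimate dropout, with the error on the favourable side.

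**Working it through.** **Inputs, all from the Sample size section:** p = 0.15, n = 60 (both arms together), 95% confidence (z = 1.96), stated margin 8.4.

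**Consistency of the inputs.** 15% of 60 is 9 dropouts, which leaves 60 − 9 = 51, the plan's own number of completers. So 15% and 60 are the figures in use.

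**Attempt to reproduce the plan's figure.** Normal-approximation half-width:

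z × sqrt(p(1 − p)/n) = 1.96 × sqrt(0.15 × 0.85/60) = 1.96 × sqrt(0.002125) = 1.96 × 0.0461 = 0.0904.

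That is ±9.0 percentage points, an interval of 6.0% to 24.0%. The stated ±8.4 would give 6.6% to 23.4%. The difference is 9.04 − 8.4 = 0.64 points.

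**Other readings of the unit.** In participants, the margin would be 0.0904 × 60 = 5.4, which is not 8.4 either.

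**Other 95% methods at p = 0.15, n = 60 (half-widths in points):**

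| Method | Half-width |
|---|---|
| Jeffreys | 8.95 |
| Wilson (8.1% to 26.1%) | 9.01 |
| Logit | 9.20 |
| t quantile in place of z | 9.22 |
| z rounded to 2 | 9.22 |
| Agresti-Coull | 9.24 |
| Clopper-Pearson (7.1% to 26.6%) | 9.74 |
| Normal with continuity correction | 9.87 |

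The smallest of these is 8.95.

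**Changing an input.** With 51 completers in place of 60, the normal half-width is 9.80, further away. A 90% level gives 7.58 with n = 60 and 8.22 with n = 51. Working backwards from 8.4, one of the following would be needed:

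- n = 1.96² × 0.1275/0.084² = 69.4 (n = 69 gives 8.43, n = 70 gives 8.36);
- a dropout rate of about 12.6% with n = 60;
- a confidence level of about 93.2% with n = 60 and 15%.

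None of these matches what the sentence says.

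**Per arm, for information only.** With n = 30: 1.96 × sqrt(0.1275/30) = 0.128, or ±12.8 points. The protocol prints no figure to compare with this.

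**The case against.** The best defence is that the gap is small and the text calls the margin approximate. The statement is also supplementary: it follows the HAM-D-17 comparison and the recommended range of 24 to 50 participants, and N = 60 was not derived from it. The dropout criterion is a plain threshold on the observed rate, so no margin enters the decision. All of this stands, and it is why the point is minor. It does not rescue the number. Approximate fits the use of a normal approximation, but that approximation gives 9.0, and so, to within rounding or more, do the alternatives.

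A reader might infer more than the protocol supports in three ways.

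- **A shortage of participants.** Since 8.4 fits about 70 participants, it is tempting to say that the trial is about 10 short. But the protocol nowhere sets ±8.4 as a target; it only reports the precision that 60 would give.
- **A second error for the active arm.** It can be argued that tolerability of active stimulation is best read in the active arm, particularly as the objectives hypothesise no difference in dropout between groups. But the margin is tied explicitly to the sample of 60, the analysis plan summarises overall dropout, and the success criterion names no arm. The ±12.8 contradicts nothing in the text.
- **The origin of 8.4.** A sample of 69 or 70, or a rate near 12.6%, would fit equally well. The protocol does not show which, if any, was used.

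**Conclusion.** The figure is wrong as written. For 15% dropout, 60 participants and 95% confidence, the margin is ±9.0 percentage points, so the stated precision is about 0.6 points too favourable (9.04/8.4 = 1.076, about 8% too narrow a margin). This rests only on the inputs in the sentence itself and on reading 8.4 as percentage points.

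The severity is minor. The correction changes no analysis, leaves the success threshold as it is, and gives no reason to alter N = 60. Whether the other grounds given for 60 participants hold is a separate question that this check does not address. The success criterion contains no miscalculated figure and is not a second location of the error.

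**What to change.** In the Sample size section, replace ±8.4 with ±9.0 percentage points (normal approximation), so that both the unit and the method are stated.

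If an exact interval is also wanted, name it: Clopper-Pearson 95% interval 7% to 27% if 9 of 60 participants drop out. The label matters, because a symmetric ±9.0 implies 6% to 24%, and the two would look inconsistent side by side without it.

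Optionally, add that the margin within one arm of 30 would be about ±12.8 percentage points.

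The cost is one edited sentence and a slightly less favourable figure. Nothing in the design, conduct or analysis changes.
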